### Plans for collection, laboratory evaluation and storage of biological specimens for genetic or molecular analysis in this trial/future use {33}

Aliquots of blood, bubo aspirates and sputum samples will be stored initially at the site and then transported to IPM. Sample custody will be maintained by the investigators, and decisions regarding the use and transfer of samples to the research laboratory will be made by the TOC. Biological research samples will be stored indefinitely, and approval from the sponsor and/or ethics committees, as appropriate, will be sought prior to destruction.

#### Rapid diagnostic test (RDT) for plague at admission

The bubo will be aspirated, and a RDT for plague will be performed on site. This RDT for the detection of the F1 antigen of *Y. pestis* is manufactured by IPM. The test has been used routinely over the past decade and has been validated for bubonic plague. Site staff, clinical research associates and clinical study nurses will be trained on the use and interpretation of the RDT before the start of the study and during annual retraining.

#### At the central plague laboratory (CPL) level

The remaining bubo aspirate will be stored in Cary Blair transport medium, packed according to the required safety level using the materials already provided (triple packaging), then sent to the CPL at IPM for a second RDT analysis as well as for molecular and bacteriological diagnosis. Molecular diagnosis will first be performed by real-time PCR (qPCR) targeting 2 fragments of the *pla* and *caf-1* genes of *Y. pestis*, and only samples with inconclusive results will be confirmed by conventional PCR (cPCR) targeting 3 genes *pla*, *caf-1* and inv1100. Bacteriology will be done with direct culture and amplification in mice followed by biochemical identification of the suspected strain by API 20E and by bacteriophage lysis test, then antibiotic susceptibility testing of each *Y. pestis* isolated strain according to the Kirby Bauer method interpreted according to the CLSI reference.

Sputum samples will not be tested on site with RDT but will be sent directly to the CPL. Biological results will be sent back to the physician responsible for the patient.

#### Malaria

A malaria RDT will be performed on all patients at admission.

#### Serology

A 4-ml venous blood sample will be taken at admission (D1), D11 and D21 for plague serology (for children, a 2-ml venous blood sample will be taken at these time points). In addition, for subjects with positive serology at D21, serological follow-up will be carried out at 3 months (M3) after their inclusion. Two types of serological techniques will be performed: serology by immuno-enzymatic assay method (ELISA, anti-F1 antibodies, IgG) which is validated and will be performed at the CPL, and serological analysis by xMAP-Luminex multiplex technique (Magpix) to simultaneously detect antibodies (IgM and IgG) directed against several *Y. pestis* antigens will be performed at the immunology of infectious diseases unit (IMI) at IPM. A serological test (on magnetic beads, XMAP-Luminex) to detect and quantify the F1 circulating antigen of *Y. pestis* will also be performed. Only anti-F1 IgG ELISA technique will be considered for case classification.

## Statistical methods

### Statistical methods for primary and secondary outcomes {20a}

#### Primary endpoint analysis

The final classification of cases will take into account all clinical and biological data in accordance with WHO recommendations adapted in 2017 with the introduction of qPCR as a diagnostic tool [3, 11].

The data will be analyzed using four analysis populations: (i) intention to treat (ITT), (ii) intention to treat infected (ITTI), (iii) per-protocol (PP) and (iv) per-protocol infected (PPI). Intention to treat infected (ITTI) will be the primary analysis population. An infected patient is a confirmed or probable case. A case is probable if the RDT or qPCR or serology (anti-F1 IgG ELISA) is positive but without evidence of seroconversion or a fourfold increase in antibody titre. A case is confirmed if the RDT and qPCR are positive or if the culture is positive or if there has been a seroconversion or a fourfold increase in antibody titre on two separate serological samples (either between D1 and D11, between D11 and D21 or between D1 and D21).

The criteria for exclusion from the per-protocol analysis population will be specified in advance in the statistical analysis plan (SAP). The proportion of patients who meet the pre-established definition of therapeutic response in the streptomycin plus ciprofloxacin group will be subtracted from the proportion of patients who meet the pre-established definition of therapeutic response in the ciprofloxacin group. A positive difference in proportions would imply a higher response in patients treated with ciprofloxacin, compared to streptomycin plus ciprofloxacin, and a negative difference would imply a lower response in patients treated with ciprofloxacin. If the lower limit of the one-sided 2.5% confidence interval (CI) around the difference in proportions is not less than − 0.15, ciprofloxacin will be considered non-inferior to streptomycin plus ciprofloxacin.

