#### Box 1—Case definitions

**Table Tabb:** 

Probable and confirmed cases are defined as:	
Probable case: rapid diagnostic test (RDT) or qPCR or serology (anti-F1 IgG ELISA) is positive but without evidence of seroconversion or a fourfold increase in antibody titre.	
Confirmed case: RDT and qPCR are positive, or culture is positive, or there has been a seroconversion or a fourfold increase in antibody titre on two separate serological samples (either between D1 and D11, between D11 and D21 or between D1 and D21).	

We will recruit patients with clinical suspicion of bubonic plague, but the size of our sample is powered based on an intention to treat infected patient sample size of 190, where ‘infected’ is defined as a ‘confirmed’ or ‘probable’ case of bubonic plague. As a result, the total number of patients to be enrolled will be higher than 190. We estimate that we will need to recruit approximately 600 patients with bubonic plague to achieve a sample size of 190 confirmed/probable bubonic plague patients. However, to mitigate risks of being under-powered, we will recruit for three full seasons (2019–2022) with a minimum target of 190 confirmed/probable cases, 95 patients in each arm.

Should we achieve the target of 190 confirmed/probable bubonic plague cases before the end of the third season (2019–2022), we will nevertheless continue to recruit until the end of the season to retain power in the event the observed treatment success rates differ from those expected, and to allow us to increase precision.

Whilst we will also recruit and collect data on patients with pneumonic plague, it is highly unlikely that we will have the power to complete a non-inferiority trial for ciprofloxacin monotherapy for pneumonic plague patients. For example, with a case fatality rate of 20–25%, we would need a sample size of approximately 400 patients with probable/confirmed pneumonic plague for a non-inferiority margin of 15%, which is unrealistic.

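### Entry to the primary population (ITTI) depends partly on serology drawn on or after the endpoint day: add a supportive set defined by day-1 tests and remove the clinical input to classification

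*Protocol article*

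**What the plan says.** Under Primary endpoint analysis the protocol article states: "Intention to treat infected (ITTI) will be the primary analysis population". Infected means confirmed or probable. Only the per-protocol exclusions are left to the SAP, so the ITTI rule is fixed in this document.

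There are two serological routes into ITTI:

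- **Confirmed:** "if there has been a seroconversion or a fourfold increase in antibody titre on two separate serological samples", with the pairs given as "either between D1 and D11, between D11 and D21 or between D1 and D21".
- **Probable:** "A case is probable if the RDT or qPCR or serology (anti-F1 IgG ELISA) is positive", without limiting the serology to D1.

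Box 1 (Case definitions) gives the same rules. The Serology section sets the timing: "A 4-ml venous blood sample will be taken at admission (D1), D11 and D21 for plague serology". The bubo RDT, PCR and culture are D1 tests (Table 2).

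The paragraph that contains these definitions opens with "The final classification of cases will take into account all clinical and biological data". No clinical criterion appears in the definitions themselves.

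**The concern.** Each pair of serological samples needs one taken at D11 or D21. D11 is the day on which the primary endpoint is assessed, and D21 comes after it. Being alive is a component of that endpoint. For an infected patient negative on all D1 tests (RDT, qPCR, culture, ELISA), membership of the primary population therefore requires being alive and sampled on or after the endpoint day. An early death in this group is a treatment failure that the primary analysis never sees. If such events are more frequent on ciprofloxacin, their removal narrows the observed difference, and in a non-inferiority trial that is the unsafe direction.

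The word clinical in the opening sentence is a separate, smaller problem. Clinical data collected up to D21 include the response to treatment, and patients and the trial team know the allocation. Read literally, the sentence allows an input to classification that the operative rule does not contain.

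**Working it through.** **1. The plan's own figure.** Inputs from Sample size {14}: 90% response in both arms, margin 0.15, one-sided 2.5%, power 90%, 10% loss.

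n per arm = 2 × 0.90 × 0.10 × (1.960 + 1.282)² / 0.15² = 84.06, rounded up to 85. Then 85 / 0.90 = 94.4, rounded up to 95, or 190 in total. The stated figure reproduces.

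**2. Who can drop out.**

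| Infected patient | Sampled at D11 or D21 | Dies or is lost with no later sample |
|---|---|---|
| Positive on any D1 test | in ITTI | in ITTI |
| Negative on all D1 tests | in ITTI if serology qualifies | cannot enter ITTI |

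Only the bottom right cell is affected.

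**3. Size, by share of failures that come early.** Assumptions, none of them in the documents: true response 0.90 (control) and 0.75 (ciprofloxacin), which is exactly at the margin; 95 infected per arm; a share q detectable only by later serology; a share g of that group's failures occurring before the second sample.

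- Retained fraction in an arm: k = 1 − (1 − p) × q × g
- Observed response: p / k, with n = 95 × k
- One-sided error: Φ[(observed difference + 0.15) / SE − 1.96], unpooled normal approximation

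Example, q = 0.20 and g = 0.5: k = 0.990 and 0.975; observed response 0.9091 and 0.7692; difference −0.1399; SE 0.0529; Φ(0.0101 / 0.0529 − 1.96) = Φ(−1.768) = 3.9%. On average about 1.0 control and 2.4 ciprofloxacin patients are removed.

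| q | g = 0.25 | g = 0.5 | g = 1 (bound) |
|---|---|---|---|
| 10% | 2.8% | 3.1% | 3.9% |
| 20% | 3.1% | 3.9% | 6.1% |

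With 85 instead of 95 per arm, the 6.1% becomes 5.8%.

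**4. Direction.** Step 3 builds in an imbalance: early loss in the serology-only group is 0.10g on control and 0.25g on ciprofloxacin. To free the direction, set early death or loss (counted as failure) to e in each arm separately, and let a serology-only share s of those patients leave. Observed response is then p / (1 − s × e).

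- Equal early loss, 5% in both arms, s = 20%: 0.90 / 0.99 = 0.9091 and 0.75 / 0.99 = 0.7576; difference −0.1515; error 2.3%. Across s = 10-50% the error is 2.4% to 2.1%.
- Early loss 5% on control and 15% on ciprofloxacin: s = 10% gives a difference of −0.143 and an error of 3.4%; s = 20% gives −0.136 and 4.5%.

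Equal loss magnifies the true deficit slightly and is conservative. Sufficiently unequal loss against ciprofloxacin is not.

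**5. Power of a set defined by D1 tests.** At 90% response in both arms, power = Φ(0.15 / √(0.18 / n) − 1.96). With n = 85 it is 90%. If 10% leave (n about 77) it is 87%; if 20% leave (n = 68), 83%; if 30% leave (n = 59.5), 78%.

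**The case against.** The strongest reply concerns size. Persistent fever, too little bubo reduction, alternative treatment and continued antibiotics are also failures, and such patients can be alive at D11, the day the serology is drawn. Only deaths and losses can disappear, so g = 1 is an extreme. This stands, and the 6% is given only as a bound.

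The second reply concerns direction. A reader might infer that this selection always helps ciprofloxacin. It does not: with equal early loss it is slightly conservative. In addition, the missing-data rule {20c} counts a patient lost after showing fever resolution and sufficient bubo reduction on or after day 4 as a responder. If that patient was D1-negative and has no later sample, a success is removed. This also stands.

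Third, a reader might infer from "The final classification of cases will take into account all clinical and biological data" that staff can move patients in or out according to outcome. The documents do not support that. The laboratory definitions are stated twice, assays are done centrally, and routine bubo samples carry no trial identifier (Participant confidentiality). What remains is an inconsistency of wording that could matter only if clinical judgement were used at final classification.

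Fourth, since a case is probable when "serology (anti-F1 IgG ELISA) is positive but without evidence of seroconversion", a reader might infer that past infections dilute the primary comparison by a known amount. The documents give no background seroprevalence, no share with stable IgG only and no response rate for such patients, so no size can be attached.

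Finally, ITT, PP and PPI analyses are planned, and blinding of classification may be in the SAP. ITT is free of this selection, but about 410 of the 600 enrolled (600 − 190) would not be confirmed or probable cases, so it is a diluted check on a non-inferiority claim.

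**Conclusion.** The point holds in limited form. As written, the primary population is partly selected on an event after randomisation that overlaps the endpoint, and the sentence introducing the rule conflicts with the rule. The selection acts only on infected patients negative on all D1 tests, and it favours non-inferiority when early death or loss is more frequent on ciprofloxacin.

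Under the assumptions in the working, the one-sided error is about 2.8-3.9% for a serology-only share of 10-20% with a quarter to a half of failures early. It is about 6% as an upper bound at 20%, and 2.1-2.4% with equal early loss. These figures rest on assumed shares, on true rates exactly at the margin and on a normal approximation.

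A reader might conclude that ITTI must be replaced as the primary population. The documents do not support going that far: the serology-only share is unknown, the effect at moderate shares is small, and replacement would cost power in the confirmatory test. This is an inexpensive improvement and does not invalidate the design.

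**What to change.** - Delete the word clinical from the opening sentence of Primary endpoint analysis, so that infected status follows the stated laboratory rule only.
- State that classification is locked blind to arm and outcome. If the SAP already does this, refer to it.
- Keep ITTI as primary. Pre-specify, as a named supportive analysis of the non-inferiority claim, ITTI restricted to patients positive on D1 specimens (RDT, qPCR, culture or D1 ELISA).
- Report by arm the number of serology-only patients in ITTI, and the deaths and losses before D11 among D1-negative patients. These counts show whether early loss was balanced.

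Cost: wording and one extra analysis, using specimens and visits already scheduled. The supportive analysis has lower power, about 87% if 10% of evaluable patients are serology-only and 83% if 20% are, so its interval should be read with that in mind. The primary sample size of 190 does not change.

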#### Analysis of secondary endpoints

Descriptive summaries of the data will be provided by randomization arm for the pre-specified secondary outcomes. The data will be summarized by randomization arm using the mean (95% Cl) and median (interval) for continuous or discrete data and raw data with percentages and 95% CIs for binary variables. The average time to resolution of fever and pain at the bubo site will also be summarized.

### Interim analyses {21b}

No formal interim analysis is planned. It is unlikely that the trial can be stopped prematurely, as a smaller sample will not provide the precision required to demonstrate non-inferiority within the pre-specified margin.

### Methods for additional analyses (e.g. subgroup analyses) {20b}

No additional analyses are planned.

### Methods in analysis to handle protocol non-adherence and any statistical methods to handle missing data {20c}

#### Missing data handling: primary endpoint

If a patient has had a resolution of fever and shows a ≥ 25% reduction in bubo size on or after day 4, but is lost for follow-up before day 11, he or she will be considered to have had a therapeutic response.

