### Trial design {8}

#### Study schematics

This is an individually randomized two-group parallel arm control trial with a 1:1 ratio. Patients will be randomized to receive either streptomycin + ciprofloxacin or ciprofloxacin alone. We are using a non-inferiority design since the overall cure rate for bubonic plague without septicaemia with streptomycin is expected to be 90%. As a result, demonstrating superiority would be unnecessary and impractical given the sample size that would be required. Our aim is therefore to demonstrate that ciprofloxacin alone is not more than 15% inferior to streptomycin followed by ciprofloxacin (15% is the non-inferiority margin in our study, meaning that the lower bound of the confidence interval around the risk difference in the success rates of streptomycin + ciprofloxacin and ciprofloxacin alone must not include 15%). The trial is powered for bubonic plague, although we will recruit patients with pneumonic plague as well.

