### Outcomes {12}

#### Primary endpoint

The proportion of patients with bubonic plague with a therapeutic response (assessed on D11). Therapeutic response is defined as follows for subjects with a visible and measurable bubo:
AliveResolution of fever (uncorrected axillary temperature < 37.5 °C)A ≥ 25% decrease in bubo size (in the case of multiple buboes, the largest bubo)Has not received alternative treatment for plagueNo clinical decision to continue anti-plague antibiotics beyond day 10

For patients with small buboes that are palpable but not measurable:
AliveAbsence of fever (uncorrected axillary temperature < 37.5 °C)Bubo has not enlargedHas not received alternative treatment for plagueNo clinical decision to continue anti-plague antibiotics beyond day 10

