### Sample size {14}

Assuming that 90% of individuals receiving streptomycin plus ciprofloxacin (control treatment) meet the primary endpoint definition of therapeutic response on day 11, 190 confirmed/probable bubonic plague patients (95 per group) would be required to have 90% power to demonstrate the non-inferiority of ciprofloxacin treatment compared to streptomycin plus ciprofloxacin, with a 15% non-inferiority margin and a one-sided confidence interval of 2.5%. This calculation takes into account a 10% loss to follow-up rate by the end of treatment. In total, approximately 600 suspect patients will have to be recruited to obtain a sample size of 190 confirmed/probable patients.

Table 3 shows the total sample sizes (both arms) for confirmed/probable bubonic cases to demonstrate non-inferiority with 90% power, 2.5% one-sided test and assuming 10% loss to follow up, based on treatment success in the streptomycin and ciprofloxacin group and the non-inferiority margin.

**Table 3 Tab3:** Total sample sizes (both arms) for confirmed/probable bubonic cases

Therapeutic response*	Margin (%), unilateral confidence interval of 2.5%, loss of 10%, power 90%										
	5	6	7	8	9	10	11	12	13	14	15
**0.95**	890	618	454	348	276	224	186	156	134	114	100
**0.90**	1684	1170	858	658	520	424	350	294	250	216	**190**
**0.85**	2384	1656	1216	932	736	596	494	416	354	306	268
**0.80**	2990	2076	1528	1170	926	750	618	520	444	384	334
**0.75**	3506	2434	1790	1370	1084	878	726	610	520	450	392

*Proportion of “therapeutic response” in the streptomycin and ciprofloxacin group

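### The missing-data rule scores some patients lost before day 11 as responders on two of the endpoint's five components, which can draw the arms together in the non-inferiority test

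*Protocol article*

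**What the plan says.** The Outcomes section gives the primary endpoint as "The proportion of patients with bubonic plague with a therapeutic response (assessed on D11"). For a measurable bubo, response has five components: alive, afebrile, bubo smaller by at least 25%, no alternative plague treatment, and no decision to extend antibiotics past day 10. For a bubo that can be felt but not measured, the size component becomes absence of enlargement.

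Section {20c} then fixes one rule for missing primary outcomes. It applies to a patient with resolved fever and at least 25% bubo shrinkage on or after day 4. If that patient "is lost for follow-up before day 11, he or she will be considered to have had a therapeutic response".

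Table 1 schedules bubo size on days 1, 4, 11 and 21, and vital signs on days 1 to 4, 11 and 21. The rule feeds the primary comparison in the infected intention-to-treat (ITTI) population, where the lower confidence limit is held against −0.15. On expected loss, the Sample size section states: "This calculation takes into account a 10% loss to follow-up rate by the end of treatment".

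**The concern.** The rule turns an incomplete observation into a full success. Day 4 is the only scheduled bubo measurement between baseline and day 11, so the imputed success rests in practice on day-4 values. On day 4 dosing moves to the home, with six days of the course still to run. An undetected death, or undetected treatment elsewhere, after that point would be counted as a response.

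In a superiority trial, a rule that makes the arms look alike is usually conservative. In a non-inferiority trial it works the other way. If similar shares of both arms are scored as successes regardless of treatment, a true deficit of ciprofloxacin looks smaller than it is, and the chance of wrongly declaring non-inferiority rises above the planned 2.5%.

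**Working it through.** **Inputs from the protocol article (Sample size):** control response 90% ("Assuming that 90% of individuals receiving streptomycin plus ciprofloxacin (control treatment) meet the primary endpoint definition of therapeutic response on day 11"), margin 0.15, one-sided 2.5%, power 90%, 10% loss, 95 per arm. **Assumptions:** a true ciprofloxacin rate of 75% (the margin boundary), the same true rates in lost and followed patients, and the shares of lost patients who meet the day-4 rule. The article gives no such shares.

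**1. The plan's own figure.** n per arm = (1.960 + 1.282)² × 2 × 0.90 × 0.10 / 0.15² = 84.06, so 85. Inflated for loss: 85 / 0.90 = 94.4, so 95 per arm and 190 in total. This reproduces.

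**2. Endpoint and rule side by side.**

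| Day-11 component | Required by the rule? |
|---|---|
| Alive | Not stated |
| Afebrile | Yes, on or after day 4 |
| Bubo at least 25% smaller | Yes, on or after day 4 |
| Bubo not enlarged (non-measurable buboes) | Not provided for; a 25% reduction cannot be shown |
| No alternative treatment | Not stated |
| No antibiotics decided beyond day 10 | Not stated; unknowable if lost before day 10 |

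**3. Error formula.** For scored rates pS (control) and pC (ciprofloxacin), error = Φ[(pC − pS + 0.15)/SE − 1.96], with SE = √[pS(1 − pS)/95 + pC(1 − pC)/95]. Without imputation (0.90 v 0.75), SE = 0.0540 and the error is 2.5% (2.8% by exact binomial enumeration of the same Wald rule).

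**4. Upper figure: every lost patient scored a success, loss L equal in both arms.** pS = 0.90(1 − L) + L and pC = 0.75(1 − L) + L.
- L = 5%: 0.905 v 0.7625, difference −14.25 points, error 3.4%.
- L = 10%: 0.910 v 0.775, difference −13.5 points, SE 0.0519, error 4.7% (exact 5.4%).
- L = 15%: 0.915 v 0.7875, difference −12.75 points, error 6.5%.

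Only 10% is the plan's loss rate; 5% and 15% are assumed.

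**5. The rule as written: only day-4 responders imputed.** Let shares sS and sC of the lost meet the rule, and score the other lost patients as failures. At L = 10%, pS = 0.81 + 0.10 sS and pC = 0.675 + 0.10 sC, so the scored difference is −0.135 + 0.10(sC − sS). It is unbiased only if sC is 15 points below sS.
- sS = sC = 50%: 0.860 v 0.725, difference −13.5 points, error 4.4%.
- 50% v 40%: 0.860 v 0.715, difference −14.5 points, error 3.0%.
- 90% v 75%: 0.900 v 0.750, difference −15.0 points, error 2.5%.

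The article does not say how the other lost patients are scored. If they are excluded instead, equal 50% shares give 0.86/0.95 v 0.725/0.95, a difference of −14.2 points and an error of 3.5%.

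**6. Unequal loss, all lost imputed.** Loss of 5% in control and 10% in ciprofloxacin: 0.905 v 0.775, −13.0 points, error 5.7%. Loss of 15% in control and 5% in ciprofloxacin: 0.915 v 0.7625, −15.25 points, error 2.2% (exact 2.6%).

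**7. The opposite rule, missing scored as failure, 10% equal loss.** 0.81 v 0.675, again −13.5 points, error 4.3%. If both true rates are 90%, each arm scores 81% and power falls to about 75%.

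**The case against.** The strongest reply is that the rule is conditional. A regimen truly 15 points worse would plausibly have fewer day-4 responders, so conditioning on day 4 carries much of the arm difference into the imputed values. This stands. A reader might infer that the rule shrinks any true deficit of ciprofloxacin; steps 5 and 6 show that it need not.

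Second, a reader might infer that every patient who leaves after day 4 and then dies or is treated elsewhere becomes a success. The documents do not support that. The rule covers patients lost to follow-up, and it does not say that it overrides known facts. Home treatment visits with records, mobile phones, use of medical records for those who stop trial treatment, and serious adverse event reporting to day 21 are all planned. Undetected events remain, and the article does not say that known events take precedence.

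Third, one might see a conflict with the sample size, which inflates for loss as if lost patients gave no outcome. That is conservative planning and does not commit the analysis to excluding them.

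Fourth, one might conclude that nothing would expose the problem, because the article plans no additional analyses. That statement stands under the heading for subgroup-type analyses ({20b}), and sensitivity analyses may be in the SAP, which is not shown.

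**Conclusion.** The concern holds in limited form. The article itself fixes a rule for the primary endpoint that asks for two of five day-11 components, relies in practice on day-4 values, and cannot be met by patients with non-measurable buboes. This is a stated rule, not a detail left to the SAP.

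At true rates of 90% v 75%, 95 per arm and 10% equal loss, the one-sided error runs from 2.5% to about 4.7%. The lower end needs day-4 response among the lost to differ by arm as the true rates do, with the other lost patients scored as failures. The upper end scores every lost patient a success and is a bound for equal loss when the ciprofloxacin share is no higher than the control share. The shares are assumptions throughout, and unequal loss can push the error above this range or remove the inflation. An SAP sensitivity analysis would show how fragile the result is, but it would not change the primary estimate.

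**What to change.** Do not use the day-4 rule as the primary handling of missing day-11 outcomes. Instead:

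- State that any known death or alternative plague treatment is a failure and overrides imputation.
- Recover day-11 components, where traceable, from the day-21 visit, medical records and the home treatment records already planned.
- Multiply impute the remaining ITTI outcomes within arm from day-1 to day-4 data, with bubo criteria that match both endpoint definitions (measurable and non-measurable).
- Keep the day-4 carry-forward rule as a sensitivity analysis, next to a tipping-point analysis that varies the assumption by arm, up to lost ciprofloxacin patients failing and lost control patients responding.

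Do not simply switch to missing as failure, which also dilutes the difference (step 7). Multiple imputation rests on its own untestable assumption, that outcomes are missing at random given the early data; the tipping-point analysis is there to probe it.

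The cost is a change of wording in the protocol and SAP, a little more analysis work and a slightly wider interval. No extra patients or visits are needed.
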